## STUDY DESIGN

This trial is a randomised, open label evaluation of clinical and parasitological responses to directly observed treatment for uncomplicated *P. vivax* malaria. Patients with uncomplicated *P. vivax* malaria infection who meet the study inclusion criteria will be enrolled, randomised, and treated on site with either AL or CQ with or without PQ, and monitored for 12 months. The drug administration will be directly observed. The follow-up will consist of a fixed schedule of check-up visits and corresponding clinical and laboratory examinations. On the basis of the results of these assessments, the number of adverse events and number of relapses will be compared between the study arms.

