- **Primaquine:** 0.25 mg/kg daily for 14 days will be administered on days 2-16 to those with a confirmed normal G6PD test by NADPH fluorescent spot test, which is the most commonly used test and is currently recommended by the International Committee for Standardization in Hematology.

| Body weight (kg)   | mg                 | Number of 15mg tablets |
|--------------------|--------------------|------------------------|
|                    | based on 0.25mg/kg | PER DAY FOR 14 DAYS    |
| 5-14               | 1.25 to 3.5        | ¼                      |
| 15-24              | 3.75 to 6          | ¼                      |
| 25-34              | 6.25 to 8.5        | ½                      |
| 35 -60
And more | 8.75 to 15         | 1                      |

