## **Intervention or treatment**

**Antimalarial Therapy-** All patients will be randomized to receive AL or CQ. Once G6PD results are available, those testing normal will be randomized to PQ or no PQ.. In Ethiopia G6PD deficiency is very rare (0.5-2.9%) [38]. All doses of CQ, PQ, and morning AL will be given under supervision by the staff. The evening dose of AL will be given to the patients to take at home. Children less than 5 years of age will be given an extra evening dose in case of vomiting. Patients will be observed for 60 minutes after treatment for adverse reactions or vomiting. Those patients vomiting their medication within the first 30 minutes will receive a repeat full dose, those vomiting from 30-60 minutes will receive half dose. This is standard practice for anti-malarial treatment.

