### **Laboratory Evaluations:**

2. Urine pregnancy test will be conducted on all women aged 13-49 and anyone testing positive will be excluded.
3. Those enrolled will have a second finger prick performed to assess for the following:
  - Thin smear will be used to verify parasite species and thick smear to conduct a formal parasite count. Two qualified microscopists will read all the slides independently. Blood smears with discordant results (differences between the two microscopists in species diagnosis, in parasite density of > 50% or in the presence of parasites) will be re-examined by a third, independent microscopist, and parasite density will be calculated by averaging the two closest counts.
  - Hemoglobin measurement (HemoCue™ Hb 301HemoCue, Angelholm, Sweden) will be carried out and those with hemoglobin <8g/dL will be excluded.
  - Filter paper will be obtained for the purpose of genotyping to differentiate identical vs. different genotypes, potential molecular testing for resistance markers, and gametocyte testing. G6PD testing using the NADPH fluorescent spot test will be conducted at the end of each day. The NADPH fluorescent spot test is a qualitative test and those determined to be G6PD deficient will not be given primaquine.
4. Patients testing smear positive for Pv will receive AL, at one site and CQ at the other site. After G6PD testing results are available, the patients not found to be G6PD deficient will be randomized to either AL alone or AL+PQ at one study site and CQ alone or CQ+PQ at the other site. Those found to be G6PD deficient will remain in either the AL or CQ alone arms. The study will not be blinded, although microscopists reading blood films will not be aware of which arm a participant is from.
5. On day 0, each patient will receive the morning dose of treatment (AL or CQ) medication under direct observation and will be monitored for vomiting for 60 minutes. The patient or parent will be given the evening dose (for AL only) to administer at home. Each patient will return on days 1 and 2 (and up to 14 days for those in the PQ arms) for subsequent doses. Those in the primaquine arms will return on every second day on days 2-16 for directly observed therapy. Clinical reassessments will be made on days 1- 3, 7, 14, 21, 28, 35, 42, and then monthly (see Annex V and VI for a table of scheduled procedures).

Participants will be given 35 Ethiopian Birr for each visit to cover their travel expenses (this is

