**ANNEX V Schedule of follow-up activities**

|                                                                                             | Days |   |     |     |   |   |     |   |   |    |    |    |     |    |    |     |     |     |      | Months |  |
|---------------------------------------------------------------------------------------------|------|---|-----|-----|---|---|-----|---|---|----|----|----|-----|----|----|-----|-----|-----|------|--------|--|
|                                                                                             | 0    | 1 | 2   | 3   | 4 | 5 | 7   | 8 | 9 | 10 | 11 | 12 | 14  | 15 | 16 | 28  | 35  | 42  | 2-11 | 12     |  |
| Medical history, previous medication, physical examination, consent                         | X    |   |     |     |   |   |     |   |   |    |    |    |     |    |    |     |     |     |      |        |  |
| Pregnancy testing (if female age 13-49 years)                                               | X    |   |     |     |   |   |     |   |   |    |    |    |     |    |    |     |     |     |      |        |  |
| G6PD testing (Whatman 903)                                                                  |      | X |     |     |   |   |     |   |   |    |    |    |     |    |    |     |     |     |      |        |  |
| Primaquine , 14d                                                                            |      |   | X   | X   | X | X | X   | X | X | X  | X  | X  | X   | X  | X  |     |     |     |      |        |  |
| AL or CQ, 3d                                                                                | X    | X | X   |     |   |   |     |   |   |    |    |    |     |    |    |     |     |     |      |        |  |
| Vital signs                                                                                 | X    | X | X   | X   |   |   | X   |   |   |    |    |    | X   |    |    | X   | X   | X   | X    | X      |  |
| Parasite microscopy                                                                         | X    | X | X   | X   |   |   | X   |   |   |    |    |    | X   |    |    | X   | X   | X   | X    | X      |  |
| Hemoglobin                                                                                  | X    |   |     | X   |   |   | X   |   |   |    |    |    | X   |    |    | X   |     | X   |      | X      |  |

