### **Day 3, Day 7, Day 14, Day 21, Day 28, Day 35, and Day 42:**

---

Clinical assessment — referral in case of severe malaria/danger signs  
Measurement of axillary temperature  
Parasitological assessment  
Alternative treatment in case of treatment failure  
Hemoglobin/hematocrit (Day 3, 7, Day 14, Day 28, Day 42), filter paper sampling for molecular testing on any smear positive days, CQ level testing in case of treatment

failure, lumefantrine level testing on Day 7, and primaquine level testing on Day 7 and 14

Treatment with primaquine continued Days 2-16 if assigned to CQ+PQ or AL+PQ arm under direct observation

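### One sentence in Laboratory Evaluations item 5 sets alternate-day directly observed therapy for primaquine, which contradicts daily dosing and supervision of every primaquine dose; a site that followed it would leave about 4 to 5 of 14 doses unobserved.

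*Protocol*

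**What the plan says.** The primaquine entry under Drug Dosing and Regimens reads "0.25 mg/kg daily for 14 days will be administered on days 2-16".

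Four places bear on supervision:
- Study Design, in general terms: "The drug administration will be directly observed".
- Intervention or treatment: "All doses of CQ, PQ, and morning AL will be given under supervision by the staff". Only the evening artemether-lumefantrine (AL) dose is sent home. The same section adds "Patients will be observed for 60 minutes after treatment for adverse reactions or vomiting", with re-dosing rules for vomiting within 30 minutes and from 30 to 60 minutes.
- Annex VI, in the block that covers day 3, day 7 and day 14: "Treatment with primaquine continued Days 2-16 if assigned to CQ+PQ or AL+PQ arm under direct observation".
- The section on identifying and managing adverse events has children watched for an hour after each antimalarial dose.

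Laboratory Evaluations item 5 contains two adjacent sentences on attendance. The first is "Each patient will return on days 1 and 2 (and up to 14 days for those in the PQ arms) for subsequent doses". The second is "Those in the primaquine arms will return on every second day on days 2-16 for directly observed therapy".

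The Annex V row "Primaquine , 14d" marks runs of consecutive days, including days 5, 9, 11 and 15.

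**The concern.** A drug taken every day cannot be fully observed by visits every second day. The sentence therefore contradicts the supervision statements and its own neighbour. A site that books visits from it would have no instruction for the doses in between: the protocol gives no rule for dispensing primaquine to take home, no spare dose and no tablet count. For evening AL, by contrast, home dosing is spelled out, with a spare dose for children under 5.

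Primaquine versus no primaquine is the randomised contrast. For an off-visit dose, staff cannot apply the 60-minute observation or replace a vomited dose. They also cannot directly establish whether treatment was completed. Non-completion is a withdrawal criterion, and withdrawn patients leave the per-protocol analysis. Missed doses that go undetected would pull the primaquine arms towards the no-primaquine arms.

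**Working it through.** The protocol gives no count of observed or unobserved doses, so there is no figure to reproduce. The check is a count of calendar days for the initial course.

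**Inputs**
- 14 daily doses placed on days 2 to 16 (Drug Dosing and Regimens).
- First primaquine dose on day 2 (Annex VI, Day 2).
- Attendance every second day on days 2 to 16 (Laboratory Evaluations item 5, disputed sentence).
- Clinic visits within that window on days 2, 3, 7 and 14 (same item). Annex VI lists observed primaquine at the day 3, 7 and 14 visits.

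**Step 1: the window.** Days 2 to 16 inclusive are 16 − 2 + 1 = 15 days, one more than 14 daily doses need. Fourteen daily doses starting on day 2 end on day 2 + 14 − 1 = 15.

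**Step 2: days with a visit if the sentence is followed.** Alternate days from day 2 are {2, 4, 6, 8, 10, 12, 14, 16}, which is 8 days. Clinic visits add days 3 and 7, giving 10 days. The days in the window without a visit are {5, 9, 11, 13, 15}, which is 5 days.

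**Step 3: unobserved doses out of 14**

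| Placement of the 14 doses | Observed | Unobserved |
|---|---|---|
| Days 2 to 15 (day 16, a visit day, is dropped) | 9 | 5 (5/14 = 35.7%) |
| Days 2 to 16, leaving out one day without a visit | 10 | 4 (4/14 = 28.6%) |

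**Step 4: comparison.** If patients attend on every dosing day, as Intervention or treatment and Annex VI require, 0 of 14 doses are unobserved.

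**Step 5: cross-check with Annex V.** Four of the days marked for primaquine (5, 9, 11 and 15) have neither an alternate-day visit nor a clinic visit. The row shows dosing days and does not say that the doses are observed, so this is supporting evidence only.

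**Step 6: cost of daily attendance.** Days 2 to 15 are 14 visits against 10 in Step 2. Days 5, 9, 11, 13 and 15 are added and day 16 is removed, a net 5 − 1 = 4 visits per patient. At the protocol's travel payment of 35 to 50 Birr per visit, that is 4 × 35 = 140 to 4 × 50 = 200 Birr per primaquine patient.

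**The case against.** The strongest reply is that the intended rule is clear and this is a drafting slip. Intervention or treatment and Annex VI both require supervised primaquine, the adverse-event section agrees for children, and nothing provides for primaquine at home. That is largely right: the sentence is the outlier, and the harm arises only at a site that follows it. It still needs correcting, because it is an explicit instruction about when patients attend.

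Several stronger readings are tempting, and the document does not support them.
- *The disputed sentence is the only attendance rule for primaquine.* It is not. The sentence before it also sets attendance, for up to 14 days.
- *Half the course would be unobserved.* Alternate-day visits alone would leave 6 to 7 of 14 doses unobserved. That ignores the day 3 and day 7 visits, which every patient attends and at which Annex VI lists observed primaquine.
- *The shortfall can be multiplied over all 240 planned primaquine patients (2 × 120).* That assumes both sites follow the outlier. Laboratory Evaluations item 4 puts AL at one site and chloroquine at the other, so one site's error would touch one contrast and about 120 planned primaquine patients.
- *Study Design requires every dose of every drug to be observed.* It cannot mean that literally, since evening AL is taken at home. Those home doses are the same in both AL arms and do not affect the primaquine contrast.

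Two safeguards are only partial. Tracing of defaulters under Passive Surveillance finds patients who miss a visit, and no visit is due on an off-visit day. Primaquine levels on days 7 and 14 are two samples of a drug that the protocol describes as rapidly eliminated, and filter papers are analysed only after the study. They cannot prompt re-dosing. They might inform the per-protocol set, but the protocol does not say that they will.

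**Conclusion.** The contradiction is real, and the sentence is wrong as written. At a site that follows it, about 4 to 5 of 14 primaquine doses per patient (29% to 36%) in the initial course would be unobserved, against none under the supervision stated elsewhere.

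This range assumes that alternate-day attendance starts on day 2, that the day 3 and day 7 visits are used for dosing, and that all 14 doses fall within days 2 to 16. The width of the range comes from that window being one day too long.

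A reader might infer that the primaquine effect will be underestimated by some known amount, or that the trial has adopted partial supervision. The protocol supports neither. It gives no adherence rate for unobserved doses, so the effect on efficacy cannot be quantified, and its other statements point to full supervision. The sentence should be corrected, but it does not show that the design is unsound.

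**What to change.** In Laboratory Evaluations item 5, replace the disputed sentence with: *Patients allocated to primaquine attend the clinic daily on days 2–15, and all 14 doses are directly observed.* Change days 2 to 16 to days 2 to 15 in the primaquine dosing entry, in Annex VI and in the Annex V primaquine row.

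The cost is a net four visits per primaquine patient compared with alternate-day plus clinic visits (140 to 200 Birr in travel payments), plus staff and patient time. Intervention or treatment and Annex VI already imply these visits.

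If alternate-day attendance was intended, Intervention or treatment and Annex VI should instead describe partial supervision of primaquine. Off-visit doses should then be dispensed and checked by tablet count at the next visit. This avoids the extra visits but gives up direct observation and vomiting checks for 4 to 5 doses per patient.

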### **Known efficacy and adverse effects of treatment drugs**

- **Artemether - lumefantrine (Coartem or AL):** AL is currently the first line anti-malarial recommended by Ethiopian Ministry of Health for the treatment of uncomplicated falciparum infection, mixed Pf and *P. vivax* infections, and treatment of clinical malaria cases without laboratory confirmation which comprises of non-malaria cases, falciparum cases, and vivax cases. It is also an alternative medication for *P. vivax* infection when CQ is unavailable in Ethiopia. Adverse events are generally mild, most commonly gastrointestinal (GI) (vomiting and diarrhea) and hematologic (anemia and eosinophilia) [33]. Its safety was demonstrated in studies from Ethiopia and Uganda and in many other countries [34, 35].
- **Chloroquine (CQ):** Chloroquine, a 4-aminoquinoline, was recognized as an effective and safe antimalarial in 1946, and was the most widely used drug against malaria until significant resistance to chloroquine rendered it ineffective against *P. falciparum* by 1999. CQ is currently recommended by Ethiopian Ministry of Health for the treatment of *P. vivax* infection. Resistance to CQ has been described mostly in Southeast Asia in *P. vivax*, but available evidence shows relatively low levels of resistance in Ethiopia. Side effects include dizziness, skeletal muscle weakness, mild GI disturbances (nausea, vomiting, abdominal discomfort, and diarrhea), and pruritus [36].
- **Primaquine (PQ):** Primaquine is an 8-aminoquinoline and is effective against intrahepatic forms of all types of malaria parasite. It is used to provide radical cure of *P. vivax* and *P. ovale* malaria, in combination with a blood schizontocide such as CQ or AL for the erythrocytic parasites. The most important adverse effects are hemolytic anemia in patients with glucose-6-phosphate--dehydrogenase (G6PD) deficiency. In patients with the most common African variant of G6PD deficiency, the standard course of primaquine generally produces a benign self-limiting anemia. Therapeutic doses may also cause abdominal pain if administered on an empty stomach. Larger doses can cause nausea and vomiting. Methemoglobinaemia may occur. Other uncommon effects include mild anemia and leukocytosis. The severity of hemolytic anemia is related to primaquine dosing and the variant of the G6PD enzyme. Fortunately, primaquine is eliminated rapidly and so hemolysis is self-limiting provided no further drug is taken.

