9. **Molecular testing.** A filter paper blood spot will be collected on days 0 and after day 3 in case of recurrent parasitemia for an array of parasite molecular testing including genotyping, resistance drug markers, parasite genome sequencing, and for gametocytes. In *P. falciparum* malaria primaquine accelerates clearance of gametocytes and artemisinin derivatives prevent gametocyte development. However, in *P. vivax* malaria effect of these drugs on gametocyte carriage remains unclear due to limited studies. Therefore, we will examine gametocytemia by blood smear and measuring Pvs25 using reverse –transcript quantitative PCR tool in the smear positive DBS from day 0 and follow up visits. Lastly, for any patients noted to have G6PD deficiency or a greater than 2.4g/dL drop in hemoglobin, their DBS sample will be tested for genetic variants of G6PD deficiency. The molecular testing will be conducted in Addis Ababa, Ethiopia, by Ethiopia Health and Nutrition Research Institute (EHNRI). If EHNRI cannot accomplish this in a timely manner, CDC Atlanta, will serve as a back-stop institution. All samples will have the study ID number and date of collection, but no other personal identifiers. The logbook that links the study ID number to the patient will be kept at the study site locked in a cabinet when not in use during the study enrollment period. After the completion of the study, this logbook will be stored in a locked cabinet in Addis Ababa at ICAP’s office. DBSs will not be used for non-malaria-related tests including HIV.

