##### **Adequate clinical and parasitological response**

- absence of parasitaemia on day 28 (day 42), irrespective of axillary temperature, in patients who did not previously meet any of the criteria of early treatment failure, late clinical failure or late parasitological failure

*P. vivax* infections that recur after drug treatment can have 1 of 3 etiologies: 1) recrudescence, 2) reinfection, or 3) relapse arising from the dormant liver stage (hypnozoites). In order to differentiate the recurrent parasitemias as identical vs. different from the original infection, a genotypic analysis will be performed by PCR including characterizing microsatellite markers to assess recrudescence from reinfection and for drug resistance markers. Molecular testing for gametocytes will also be conducted on any smear positive days. Those who fail in the chloroquine arm will have CQ levels tested from the already collected filter paper. Lumefantrine level on day 7 will be measured for those receiving AL treatment from collected filter papers. Patients noted to have G6PD deficiency by the fluorescent spot test and those with hemoglobin drop of >2.4g/dL will undergo additional G6PD genotyping.

**Valid end-points** include treatment failure, completion of the follow-up period without treatment failure, loss to follow-up, withdrawal from study (voluntary or involuntary, and protocol violation). Loss to follow-up occurs when, despite all reasonable effort, an enrolled patient who does not attend the scheduled visits, cannot be found. Patients who withdraw from the study during the treatment period (days 0-2) will be treated with CQ according to the national policy. They will be referred back to the clinic to continue with care.

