#### **Criteria for withdrawal/protocol violation**

Patients meeting any of the following criteria will be withdrawn:

- Withdrawal of consent
- Failure to complete the treatment
- Vomiting both initial and replacement doses at any single time in the treatment (i.e. If the patient vomits both attempts to administer the morning dose that would require withdrawal; however, vomiting the initial morning dose but not the morning replacement dose would not require withdrawal), persistent vomiting
- Severe side-effects necessitating hospitalization
- Progression to severe malaria
- Occurrence during the follow-up of concomitant disease that would interfere with a clear classification of the treatment outcome
- Antimalarial (or antibiotics with antimalarial activity) treatment administered by a third party or self-medication with antimalarial (or antibiotics with antimalarial activity- Annex IV) assessed by asking participants or their caretaker at follow-up visits
- Erroneous inclusion of a patient outside of the inclusion/exclusion criteria
- Misclassification of a patient due to a laboratory error (parasitemia) leading to the administration of the rescue treatment

Patients who are withdrawn will be followed up if possible and will be censored or excluded from the analysis. The reasons for discontinuation or protocol violation will be recorded on the case report form.

**Training for personnel:** Clinicians and laboratory personnel are trained and licensed in Ethiopia. In addition, they will receive approximately 1 week additional training to review the protocol of this study. In addition to technical aspects of specific laboratory techniques and clinical assessments, training will stress the importance of confidentiality, and appropriate techniques for obtaining informed consent. Continued appropriate processes with regard to informed consent will be reinforced by intermittent observation by the supervisor. The staff will include 1-2 laboratory technicians for microscopy, and 1-2 staff persons for enrollment and clinical assessments.

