## EMERGENCY CARE

Any patient with treatment failure or recrudescence will receive quinine 10mg/kg/dose every 8 hours for 7 days. This will be given orally unless the patient has persistent vomiting, in which case the patient will be referred to the nearest hospital to receive IM/IV therapy.

Patients with signs of severe malaria (altered mental status, coma, convulsions, hemoglobin <5g/dl, respiratory distress, circulatory collapse, or abnormal bleeding), persistent vomiting or severe side effects will be hospitalized and receive parenteral therapy with artesunate (or quinine if not available) and relevant supportive treatments, according to National Guidelines.

Any participant who develops urticaria or difficulty breathing following administration of the treatment drug will be treated with diphenhydramine or chlorpheniramine and will be withdrawn from the study. In addition, patient and or their parents, caretakers and family members will be counseled that the patient should not receive additional doses of the antimalarial they were given. These patients will be treated with oral quinine for seven days as per the rescue protocol.

Adult patients and parents with children in the study will be encouraged to return to the clinic for any fever or other signs of illness on any day during the follow-up period, allowing for early detection and treatment of illness before it becomes severe. Any hospitalization which occurs during the follow-up period will be paid for by the study.

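### Patients hospitalised for a side effect can drop out of the haemoglobin comparison, and a moderate haemoglobin fall during primaquine has no stated effect on dosing

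*Protocol*

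**What the plan says.** **The haemoglobin threshold.** Item 9 of Laboratory Evaluations says that for a patient with "a greater than 2.4g/dL drop in hemoglobin, their DBS sample will be tested for genetic variants of G6PD deficiency". The text after the definition of adequate response repeats this: "those with hemoglobin drop of >2.4g/dL will undergo additional G6PD genotyping". Neither place gives any other consequence. The section on notifying participants of their results puts completion of filter-paper analysis after the end of the study.

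**The PQ course and the readings.** Drug Dosing and Regimens gives 14 daily doses on days 2-16, after a normal G6PD spot test. Item 7 of Laboratory Evaluations schedules haemoglobin on days 0, 3, 7, 14, 28 and 42 and at unscheduled visits. The drug section notes that "primaquine is eliminated rapidly and so hemolysis is self-limiting provided no further drug is taken". Methods to Minimize Risks asks patients to come back if their urine turns dark.

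**Stop rules and hospital care.** Emergency Care has one explicit rule against further doses. After hives or breathing trouble, patients are withdrawn and told that "the patient should not receive additional doses of the antimalarial they were given". The same section sends severe side effects and signs of severe malaria, including haemoglobin below 5 g/dl, to hospital. Annex II lists haemoglobinuria and severe anaemia among the severe signs.

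**Withdrawal.** One criterion is "Severe side-effects necessitating hospitalization"; progression to severe malaria is another. The consequence is: "Patients who are withdrawn will be followed up if possible and will be censored or excluded from the analysis".

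**Analysis.** The data analysis plan names two general methods. The per-protocol method leaves out withdrawn patients; the survival method keeps patients up to the day before drop-out. The haemoglobin comparison is listed under the same final analysis. So are tables of side effects, anaemia and hospitalisations by arm, and of reasons for withdrawal.

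**The concern.** Haemolysis is the PQ hazard that the drug section names as most important, and the Phase 1 safety objective compares haemoglobin between patients with and without PQ. Two features of the protocol weaken that objective.

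First, a patient hospitalised for a severe side effect, including haemolysis, is withdrawn. Later readings are then taken only where possible, and the patient may be left out of the comparison altogether. Hospitalisation for a side effect can happen in any arm. Where the cause is PQ haemolysis, though, the loss falls on the PQ arms and makes PQ look safer.

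Second, the protocol collects haemoglobin during the course and names a threshold for a notable fall, but ties that threshold only to a laboratory test whose result comes too late to guide treatment. The protocol itself says recovery depends on taking no more drug.

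**Working it through.** The plan gives no figure on this point to reproduce. The check sets its rules side by side and then sizes the effect.

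**1. PQ doses still due at each scheduled reading.** The dosing text allows 14 consecutive doses on days 2-15, or a course from day 2 to day 16 with one day skipped.
- Days 2-15: day 3 leaves 13 before and 12 after that day's dose; day 7 leaves 9 and 8; day 14 leaves 2 and 1.
- Ending on day 16: at most 13, 10 and 3.
- Ranges: 12-13 of 14 (86-93%) at day 3, 8-10 (57-71%) at day 7 and 1-3 (7-21%) at day 14.

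**2. Where a fall goes unanswered.** The only numerical level during treatment that leads to hospital care is haemoglobin below 5 g/dl. Entry requires at least 8 g/dl.
- Entry at 8: a 2.4 g/dL fall gives 8 - 2.4 = 5.6, still above 5.
- Entry at 12 (an illustration): 12 - 2.4 = 9.6. The patient could lose another 4.6 before reaching 5.

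In between, the outcome depends on whether the patient is judged to have a severe side effect or a sign of severe malaria. The adverse-event section does not grade haemoglobin falls. It directs no action beyond recording for mild reactions other than vomiting, and its examples of severe reactions do not include haemolysis.

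**3. What withdrawal does to the haemoglobin data.** Take a PQ patient hospitalised for haemolysis found at the day 7 visit.
- If excluded: no reading enters the comparison.
- If censored at withdrawal: the day 0, 3 and 7 readings stay, so the mean at the triggering visit does not shift and the 7-day endpoint is intact. The lowest point and the recovery after day 7 are lost.
- In either case: later readings are taken only where possible. No analysis plan can restore readings that were not taken.

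**4. Size of the effect on the mean, under full exclusion.**
- PQ patients: 2 arms x 120 = 240.
- G6PD deficiency: 0.5-2.9%, from the Intervention section.
- Share of deficient patients missed by the spot test: 5-20% (assumption; the protocol gives none).
- Missed deficient patients: 240 x 0.005 x 0.05 = 0.06 to 240 x 0.029 x 0.20 = 1.39.
- Extra fall d relative to other patients: 2.5-3.5 g/dL (assumption).
- Shift in the PQ mean change if k such patients are excluded: k/240 x d.
- Smallest: 0.06/240 x 2.5 = 0.0006 g/dL. Largest: 1.39/240 x 3.5 = 0.020 g/dL.

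**5. Effect on the tail.** Each excluded patient with a large fall takes 1/240 = 0.4 percentage points off the observed proportion in the PQ arms. If two patients had such falls and both were excluded (assumption), that proportion would go from 2/240 = 0.8% to 0%.

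**The case against.** The strongest reply has four parts.

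**Serious haemolysis is covered.** A reader might infer that nothing in the protocol ever stops PQ for haemolysis. The documents do not support that. Hospitalised side effects and progression to severe malaria both lead to withdrawal, which ordinarily ends study dosing, and Annex II includes haemoglobinuria and severe anaemia. PQ patients also attend every second day during the course, with an adverse-event history at every visit. This stands, and it limits the dosing gap to a moderate fall, or dark urine, that does not need hospital care. Site procedures, which are not shown, may cover part of it.

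**The safety analysis set belongs in the statistical analysis plan.** Largely so. In the data analysis plan, the instruction to use both methods is attached only to treatment failures at days 28 and 42, so exclusion is not fixed for haemoglobin. An undefined safety set is no finding here. But the withdrawal rule is a protocol rule, it speaks of the analysis without limit, and it makes further follow-up conditional. That part stands as a concern.

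**Early PQ stops are not clearly withdrawals.** A reader might infer that anyone whose PQ is stopped early is withdrawn under "Failure to complete the treatment". The end-points text places the treatment period on days 0-2: "Patients who withdraw from the study during the treatment period (days 0-2) will be treated with CQ according to the national policy". That reading would limit the criterion to AL or CQ. The point here does not rely on it.

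**The numbers are tiny, and a fall is not specific to PQ.** Both are true. A reader might count affected patients from the unscreened prevalence of deficiency and reach a larger shift, but the spot test comes before PQ, so that count does not apply. Vivax infection itself can lower haemoglobin, and anaemia is a listed effect of AL. This argues for a hold pending review rather than an automatic stop.

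**Conclusion.** The point holds as a cheap improvement. Followed as written, the withdrawal rule can remove the patients with the worst safety outcomes from the haemoglobin comparison. Separately, a moderate fall or dark urine not needing hospital care has no stated effect on the remaining PQ doses.

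The effect on mean haemoglobin change is negligible. The upper figure of about 0.02 g/dL assumes that 5-20% of deficient patients are missed by the spot test, that every missed patient falls 2.5-3.5 g/dL more than the rest, and that all of them are wholly excluded. What can be lost is the record of rare large falls, which matters most to a trial meant to support safe use of PQ. The planned tables of side effects, anaemia, hospitalisations and withdrawal reasons would still show part of it. The efficacy comparison is not threatened.

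**What to change.** 1. In Criteria for withdrawal/protocol violation, state that hospitalisation for a side effect, or stopping PQ for safety, ends study drug but not follow-up. Such patients stay in their randomised arm, with all available readings, for the haemoglobin and adverse-event analyses. The per-protocol efficacy analysis can keep its present rule.

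2. In item 9 of Laboratory Evaluations, in the matching text under the end-points and in the adverse-event section, state the following. In a PQ-arm patient, a fall of more than 2.4 g/dL from day 0, or dark urine, during the course means that the remaining PQ is held pending clinical review at the same visit. The decision to resume or stop is recorded. The 2.4 g/dL value is used only because the protocol already contains it; the sponsor's safety team may choose another.

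The cost is two sentences in an amendment, repeated where the threshold appears, and one field on the case report form. No new scheduled measurement is needed. The downside is a few shortened PQ courses kept in the PQ arms.
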